#### Informed consent

All the criteria must be satisfied for included the patient in the study.

The exclusion criteria are:
Patients aged < 18 years oldInformed consent refusalNo clinical and/or laboratory and/or radiological evidence/signs of peritonitis of any originSurgical indication for laparotomies other than midline onePregnancy

The presence of even one of these exclusion criteria does not allow the patient to participate at the study.

The subject may withdraw at will at any time. The patient may be withdrawn from the trial at the discretion of the investigator for safety concerns. If the patient withdraws or is withdrawn at any time after receiving trial product, final safety information will be obtained. Patients who are deemed during surgery not suitable included in this protocol will be withdrawn from the study. In case a subject is being prematurely withdrawn from the trial, the investigator will ensure that the procedures for the last visit are undertaken, if possible. The primary reason (adverse event, non- compliance with protocol or other) for discontinuation must be specified in the CRF. A patient withdrawn from the study will be analyzed according to evaluability of subjects for analysis.

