### Visit procedures

The randomization and the study data are collected using an online form (https://prophybiom.easycrf.cloud). The access at this form is allowed only at the participant at the study that has a username and password. Investigators who conduct follow-up assessments will not be blinded.

The study comprises of the following visits (Table 1):

**Table 1 Tab1:** Time and event chart

Nomenclature	Visit 1	Visit 2	Visit 3	Visits 4, 5, and 6
	Screening	Treatment	Discharge	Follow-up
	Screening, baseline	Surgery	Discharge	Follow-up
**Informed consent**	**√**			
**Inclusion/exclusion criteria**	**√**			
**Demographic data (sex, age, weight, height, BMI)**	**√**			
**Medical history/concomitant illness**	**√**			
**Physical examination**	**√**		**√**	**√**
**ASA classification**	**√**			
**Vital signs**	**√**	**√**		
**Body weight and height**	**√**			
**ECG (12 lead)**	**√**			
**Hematology and coagulation parameters**	**√**		**√**	
**Blood chemistry**	**√**		**√**	
**Antibiotic therapy**	**√**			
**Start of LMW heparin**	**√**			
**Concomitant medication**^**a**^	**√ continuously**			
**Start and end of surgery**		**√**		
**Site and length of incision**		**√**		
**Peritonitis grade assessment**		**√**		
**Peritoneal fluid sampling for microbiological examination**		**√**		
**Contamination assessment**		**√**		
**Intestinal resection**		**√**		
**Stoma creation**		**√**		
**Surgical complications**		**√**		
**Surgical drain placement**		**√**		
**Surgery report**		**√**		
**Time of drain removal**			**√**	
**Length of stay in hospital**			**√**	
**Post-surgical complications**			**√**	**√**
**Abdominal wall ultrasound**				**√**
**Adverse events**	**√ continuously**			

^a^This includes use of any blood transfusions that should be inserted in the CRF as type (red blood cells. FFP, platelets)

• Visit 1: Screening and baseline visit: screening of patient, baseline examination, pre-surgery assessment, informed consent

• Visit 2: Treatment visit: surgery

• Visit 3: Discharge from hospital: recording of post-surgical complications

• Visits 4, 5, and 6: Post surgery follow-up visits: at 3, 6, and 12 months post-surgery. All patients will perform an abdominal wall ultrasound to document the presence or not of incisional hernia. At the last visit, the data collected is the same of the other visits. The patients are called 15 days prior to the follow-up visit to remind them of the appointment.

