In case of any premature discontinuation of the trial, the patient will, if possible, be called in for a last visit. Even if the patient is not able to attend, the End of Trial Form must be completed.

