### Statistical analysis

Only the data of participants who complete the follow-up will be considered. Descriptive analysis will be performed for all pre-operative, operative, and follow-up information. For categorical variables, we will use chi-square test, for non-categorical one the *t*-test. The primary endpoint, % of patients presenting incisional hernia at 3, 6, and 12 months, will be analyzed between treatment groups using a logistic regression model, presenting odds ratio comparisons of the two. Surgery time, time to drain removal and length of stay in hospital will be analyzed between treatment groups using Student’s *T* test if data are normally distributed and with Mann-Whitney test if data are not normally distributed. The distribution of data will be evaluated with the Shapiro-Francia test. The number of patients who died will be analyzed between treatment groups using a chi-square test.

All statistical comparisons will be based on two sided tests with a 5% significance level.

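### A patient withdrawn for safety after the one-time operation is not kept on the 3-, 6- and 12-month hernia assessments, although withdrawal then stops no trial exposure

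*Protocol article*

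**What the plan says.** The withdrawal rules stand in the protocol article under Informed consent, after the exclusion criteria. On the investigator's side: "The patient may be withdrawn from the trial at the discretion of the investigator for safety concerns". The withdrawal is from the trial, not from a treatment, and no criteria are given. The same paragraph foresees it after implantation: "If the patient withdraws or is withdrawn at any time after receiving trial product, final safety information will be obtained". It also fixes how the reason is recorded: "The primary reason (adverse event, non- compliance with protocol or other) for discontinuation must be specified in the CRF".

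Visit procedures says what follows: "In case of any premature discontinuation of the trial, the patient will, if possible, be called in for a last visit". The content of a last visit is given there too: "At the last visit, the data collected is the same of the other visits". It therefore includes the abdominal wall ultrasound.

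Two sentences govern the analysis of these patients. Under Informed consent: "A patient withdrawn from the study will be analyzed according to evaluability of subjects for analysis". Under Statistical analysis: "Only the data of participants who complete the follow-up will be considered".

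The primary endpoint (Study endpoint) is the incisional hernia rate at 3, 6 and 12 months, assessed at visits 4, 5 and 6. Visit procedures states that the investigators who make the follow-up assessments are not blinded.

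**The concern.** A safety withdrawal rule has a purpose while exposure can still be prevented or stopped. Here the exposure is one operation. Once the abdominal wall is closed, with or without the prosthesis, leaving the trial removes no trial treatment. The remaining trial procedures are visits with physical examination and ultrasound, and the article gives no safety reason to stop those. The practical effect of a withdrawal after surgery is that the scheduled hernia assessments are replaced by at most one earlier visit.

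The decision rests with an investigator who can know the arm, on a criterion that is not defined. If the patients withdrawn this way have a different hernia risk from those who stay, or if withdrawal is more frequent in one arm, the hernia comparison can be distorted. A later choice of analysis set cannot fully repair this, because the outcomes were never observed.

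**Working it through.** **1. Does any section keep a withdrawn patient on the schedule?**

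| Section | What it provides after withdrawal | Gives 12-month hernia status? |
|---|---|---|
| Informed consent | Final safety information; last-visit procedures where possible | No |
| Visit procedures | One call-in where possible, with ultrasound; End of Trial Form | Only if the call-in falls at 12 months |
| Follow-up of adverse events | Serious events followed to outcome, with exceptions for chronic conditions, cancer and death from another event | No; this follows known events and is not a search for hernia |
| Statistical analysis | Only completers of follow-up are considered | No; the patient is left out |

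No section does so.

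**2. Is informative withdrawal plausible?** Two statements make it so. Follow-up of adverse events names allergic reaction to, infection of and migration of the mesh as expected events, and these can arise only in the mesh arm. Background and rationale names surgical site infection among the factors that affect wound healing. Neither statement says that such patients will be withdrawn.

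**3. The planned sample size.** Inputs: 50% versus 20% (Objective), two-sided 5% (Statistical analysis), 1:1 allocation (Patients recruitment). Power is not stated; 80% is assumed.

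- Uncorrected: n = [1.96·√(2·0.35·0.65) + 0.842·√(0.25 + 0.16)]² / 0.30² = 38.5, so 39 per arm.
- Continuity-corrected: (38.5/4)·[1 + √(1 + 4/(38.5·0.30))]² = 44.9, so 45 per arm, 90 in total.

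This matches the stated 90 and leaves no allowance for loss.

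**4. If withdrawal is unrelated to hernia risk.** Only power is lost. With the uncorrected formula and equal loss in both arms (assumed rates):

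| Loss | Evaluable per arm | Power | Per arm needed to keep 45 evaluable |
|---|---|---|---|
| 0% | 45 | 86.0% | 45 |
| 10% | 40.5 | 82.0% | 45/0.90 = 50 |
| 15% | 38.25 | 79.8% | 45/0.85 → 53 |
| 20% | 36 | 77.2% | 45/0.80 → 57 |

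**5. If withdrawal is related to hernia risk.** Assume a true mesh-arm rate of 9/45 = 20%, withdrawals in the mesh arm only, and withdrawn patients left out of the analysis.

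| Withdrawn | All would have herniated | None would have herniated |
|---|---|---|
| 1 | 8/44 = 18.2% | 9/44 = 20.5% |
| 3 | 6/42 = 14.3% | 9/42 = 21.4% |
| 5 | 4/40 = 10.0% | 9/40 = 22.5% |

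**6. Effect on a null comparison.** Let both true rates be 50% and let a fraction f of the mesh arm be withdrawn, all of them hernia cases. The observed mesh rate is (0.50 − f)/(1 − f).

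- f = 10%: 0.40/0.90 = 44.4%, odds ratio 0.80; chance of a significant result favouring mesh about 7%.
- f = 20%: 0.30/0.80 = 37.5%, odds ratio 0.60; chance about 20%.

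The nominal chance is 2.5%. With the arms exchanged, the same arithmetic works against the mesh.

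**7. Would a different analysis set cure it?** Not fully. Take the case of five withdrawals who would all have herniated, with 4 hernias seen among 40. An analysis of all 45 could only bound the mesh rate between 4/45 = 8.9% and 9/45 = 20.0%.

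**The case against.** The rule is permissive and does not mention wound or mesh complications. A reader might infer that visits end for patients with wound or mesh trouble. The article does not say so and points the other way: Assessments for efficacy has patients evaluated at visits 4, 5 and 6 for complications that include wound infection and reintervention. The protocol thus expects at least some of these patients to remain.

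A reader might also take the mesh-specific adverse events as withdrawal triggers and conclude that the rule favours the mesh. They are listed as expected events, not as triggers. A safety concern can arise in either arm; wound infection and fascial dehiscence are not confined to mesh patients. The direction of any bias is therefore not established.

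Nor does the rule remove late harm from the safety comparison altogether. Final safety information is required, the last visit includes the ultrasound, and serious events are followed to outcome. These safeguards stand, but they do not supply the scheduled hernia outcome.

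The illustration overlaps with the completers-only analysis, because that rule takes withdrawn patients out of the denominator. The separate part is that later outcomes are never collected. The full protocol may define evaluability, but the point does not depend on that definition.

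Finally, the rule is useful before surgery. Patients recruitment places randomisation before the laparotomy, so a safety withdrawal in that interval can still prevent exposure. Any change must preserve this.

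**Conclusion.** The concern holds in a limited form. As written, the article lets an unblinded investigator withdraw a patient from the trial for safety concerns after a completed one-time operation, and it does not keep that patient on the 3-, 6- and 12-month assessments. This is a badly fixed follow-up rule rather than a detail left to another document.

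The consequence is bias if withdrawal is linked to hernia risk or differs by arm, and lost power otherwise. The article gives no withdrawal rate and no hernia risk for withdrawn patients, so neither size nor direction can be derived. The range of 10.0% to 22.5% around a true 20% rests on one to five withdrawals, all in the mesh arm, with the extremes of all or none herniating. It shows only that with 45 per arm a handful of patients can matter. The document does not support a claim that the rule favours the mesh.

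**What to change.** Limit the investigator's safety withdrawal to the period before surgery. Add that after surgery an adverse event, a reintervention or a protocol deviation is recorded but does not end follow-up. The patient then stays on visits 4, 5 and 6 with ultrasound, unless the patient dies or withdraws consent. The patient's own right to withdraw is unchanged. The change concerns outcome collection and sets no rule for clinical care.

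Keep adverse event in the CRF as a reason for the patient's own withdrawal. Deleting it would hide why patients leave, which is needed to judge whether loss is informative.

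Reconcile the evaluability sentence under Informed consent with the completers-only sentence under Statistical analysis, so that the retained data are used.

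The cost is a wording amendment, plus the effort of retaining a few sick patients at visits that are already planned. When the article was written, six of the 90 patients had been enrolled, so the change would have covered nearly the whole trial.

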### Patients recruitment

Enrolled patients scheduled to undergo urgent/emergent laparotomy in contaminated/infected fields with peritonitis, after signing the informed consent, and before the scheduled laparotomy will be randomized (Fig. 2) to be undergone to abdominal wall closure either with mass closure technique with simple running monofilament using a long-lasting absorbable suture material or with the same technique associated to the previous retro-muscular positioning of a swine dermal collagen prosthesis (sec. Rives-Stoppa technique). The patient is identified by the surgeon that visits him/her at the arrival in ED. If the patient is eligible the same surgeon acquires consent and gives all the information about the study and the type of mesh that is used for the study. There are no ethical concerns with the randomization, because the control group will receive the standard of care treatment while the study group will receive the same treatment plus the implantation of the biological prosthesis: this prosthesis does not have reported serious side effects and it is expected to reduce the abdominal wall complication rate. If the patient allows for the study but the randomization place him in the control group, he will be treated with the standard of care (suture with running monofilament using a long-lasting absorbable suture material).

**Fig. 2 Fig2:**
[figure not shown]
Graphical flow chart

The randomization is due electronically by an online software (https://prophybiom.easycrf.cloud). The sequence of allocation has been generated by a statistician who is independent by the study. The randomization is simple and the allocation is 1:1 to each arm. The allocation sequence is accessed only when it is requested. The randomization is due electronically by the online software when the surgeon inserts the patient in the online form.

The patient is associated at an alphanumerical code that is constituted by three parts:
First, two letters indicate the center of intervention (for example PR for University Hospital of Parma, PI for University Hospital of Pisa);Second, two numbers indicate the chronological sequential number of allocation (for example 01, 02, 03, etc.);Last, letter indicates the control group (A) or trial group (B).

So, for example, a patient that has positioning of the mesh at the University Hospital of Parma could have an alphanumerical code like “PR05B.”

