### Data management

Data management is the responsibility of the principal investigator. All data relating to the various phases of the study will be collected in the appropriate electronic data collection form provided by an external company (m:gnu, Consultancy-Web Architecture-Management). The patients for whom the data is collected are cataloged with an identification code, which in the electronic version would translate into an alphanumeric code generated automatically by the system, thus avoiding the recording of personal data; in this way, the patient is de facto anonymized, and the data collected could not be considered “sensitive,” because they are not associated with an identifiable person. The cloud platforms that will be used are all GDPR compliant. The access at the anonymous data is permitted only at the principal investigator. The subject will be identified by subject number. Appropriate measures such as encryption or deletion will be enforced to protect the identity of human subjects in all presentations and publications as required by local/regional/national requirements. The data is monitoring by the principal investigator of the leader center of the study. There is a monitoring committee that monitors the data collection and study progress. This committee is the Unit of Clinical Research and Epidemiology of University Hospital of Parma. The monitoring committee monitors the data every 6 months. Statisticians, medical doctors specialized in epidemiology, and data managers are part of the monitoring committee.

When all 90 patients have been entered in the data base, data quality will be ensured and a data base release conducted.

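### Hernia is judged by assessors declared unblinded, and a patient code ending in the arm letter adds disclosure of the allocation that could be avoided

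*Protocol article*

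**What the plan says.** All references are to the protocol article.

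- **Patients recruitment (text below Fig. 2).** The patient code has three parts: centre, sequential number and arm. In the last part the "letter indicates the control group (A) or trial group (B". The worked example leaves no doubt that the letter is openly decoded: "a patient that has positioning of the mesh at the University Hospital of Parma could have an alphanumerical code like" PR05B.
- **Visit procedures.** "Investigators who conduct follow-up assessments will not be blinded". At the 3-, 6- and 12-month visits, "All patients will perform an abdominal wall ultrasound to document the presence or not of incisional hernia". The same platform handles allocation and data capture: "The randomization and the study data are collected using an online form".
- **Abstract (Methods) and Table 1.** Hernia is sought by physical examination as well as by ultrasound.
- **Data management.** Patients are catalogued by an identification code, "which in the electronic version would translate into an alphanumeric code generated automatically by the system". On oversight, "The monitoring committee monitors the data every 6 months". On access, "The access at the anonymous data is permitted only at the principal investigator".

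No section describes a masked reader, adjudication of hernia or an arm-neutral identifier, and no reason is given for leaving follow-up assessors unblinded.

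**The concern.** Deciding whether a hernia is present takes judgement, above all for small defects or bulging, and the article gives no threshold that would constrain it. The same article says, under Patients recruitment, that it expects the prosthesis to lower abdominal wall complications. An assessor who shares that expectation and knows the arm may call borderline findings differently in the two groups. That bias goes straight into the primary comparison, and a larger sample would not remove it.

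There is a second, smaller route. The Statistical analysis section keeps only participants who complete follow-up, and withdrawn patients are handled according to their evaluability. If those decisions are made on records identified by an arm-bearing code, they too can follow knowledge of the arm.

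The surgeon cannot be masked. The question is whether disclosure goes further than the design requires. The arm letter does, because it serves no purpose as an identifier.

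**Working it through.** **1. The plan's own figure.** The plan has 45 per arm (90 in total) and aims to reduce hernia from 50% to 20%, with two-sided tests at 5%. Power is not stated; 80% is assumed here.

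- Without continuity correction: n = [1.96·√(2·0.35·0.65) + 0.8416·√(0.5·0.5 + 0.2·0.8)]² / 0.30² = (1.322 + 0.539)² / 0.09 = 38.5, so 39 per arm.
- With continuity correction: n′ = (38.5/4)·[1 + √(1 + 4/(38.5·0.30))]² = 44.9, so 45 per arm.

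The stated 45 per arm is reproduced. This point does not change it, because masking alters neither the sample size nor the nominal significance level.

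**2. Is the arm letter needed?** Centre and sequence number (PR05) already identify the patient. The allocation is issued by the platform that also collects the study data, so it is held there anyway. The letter adds only disclosure.

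**3. Who is shown to know the arm?**

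| Person | What the article states |
|---|---|
| Follow-up investigators | Unblinded, stated outright |
| Anyone who handles the patient code | Arm readable from the last letter |
| Ultrasound operator | Not said who this is, or whether the code is on the request or report |
| Monitoring committee | Monitors data every 6 months; not said whether it views records by code |
| Analyst | Not addressed |

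**4. How much could it matter?** The documents give no misclassification rate, so everything in this step is an assumed illustration. Suppose the mesh has no effect, the true hernia rate is 40% in both arms, and there are 45 per arm. For x₁ and x₂ hernias called in control and mesh, let p = (x₁ + x₂)/90. The test rejects when ((x₁ − x₂)/45)² / [p(1 − p)·2/45] > 3.841. Summing the product of the two binomial probabilities over all rejecting pairs (x₁, x₂ = 0 to 45) gives:

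| Called hernia rate, control / mesh | Gap | False-positive rate |
|---|---|---|
| 40% / 40% | 0 points | 4.9% |
| 40% / 35% (mesh only under-called) | 5 points | 7.9% |
| 40% / 30% (mesh only under-called) | 10 points | 17.4% |
| 45% / 35% (opposite shifts) | 10 points | 15.8% |
| 50% / 30% (opposite shifts) | 20 points | 48.9% |

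The last row is extreme: 20 points is two thirds of the trial's 30-point target effect.

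**5. A different assumption.** Suppose instead that a share of true hernias is missed in the mesh arm only (normal approximation, 45 per arm). With 10% to 30% missed, the false-positive rate is 7.6% to 30.0% at a true rate of 50%, 6.4% to 19.2% at 35%, and 5.7% to 11.7% at 20%. With equal detection it stays at 5%.

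**6. Choice of test.** The plan analyses the primary endpoint by logistic regression, whereas step 4 uses the uncorrected chi-square. With treatment as the only term, that chi-square is the score test of the logistic model, so it is a reasonable stand-in. The article does not state any covariates.

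**The case against.** The strongest case against has four parts.

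*Scope.* A reader might infer that everyone who reads, enters or monitors the outcome knows the arm, and that the letter stands on every form, listing and ultrasound record. The article does not support that. It says a code is associated with the patient, not where the code is printed. Access to the form requires a login, and access to the anonymous data is limited to the principal investigator. Masking of the analyst is a matter commonly left to an SAP. This stands, and the point is confined to those who handle the code and to the investigators declared unblinded. The access limit is, however, a confidentiality rule that masks no assessor, and the same section has a committee monitor the data.

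*Cause.* A reader might also infer that the code removes any chance of masking. It does not: an ultrasound operator could be kept unaware by leaving the code off the request. Conversely, dropping the letter alone blinds none of the investigators whom the plan leaves open. This stands. Open assessment is the main issue and the code is secondary.

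*Feasibility.* It is tempting to say that the allocation could simply be withheld. That is true of the code but not clearly of the assessment. The Intervention section describes a retro-muscular prosthesis with at least 5 cm of overlap and at least eight fixing stitches, and the article does not say whether these show on a scan. A surgeon who knows the arm may do the physical examination, and patients may disclose their arm. Masking would therefore be partial.

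*Size.* The base rate and the shifts are assumptions, and the largest results need opposite errors in the two arms. This stands, and is why the table gives between-arm gaps and includes the one-arm cases.

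None of this explains why an identifier should carry the arm, or why a scan already planned should not be recorded without knowledge of the arm where that is possible.

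**Conclusion.** The concern holds in limited form. The plan leaves assessors of a judged primary outcome unblinded without giving a reason, and fixes a patient code that discloses the arm to anyone who handles it, with no gain in identification. This is a weakness of design that the article states openly; it is not a contradiction, and no stated figure is wrong.

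The size cannot be estimated from the documents. Under the assumptions in the working (true rate 40% in both arms, 45 per arm, uncorrected chi-square), the false-positive rate rises from 4.9% to 7.9% or 17.4% when only the mesh arm is under-called by 5 or 10 points. The 15.8% and 48.9% results apply only if errors run in opposite directions. If assessors call hernia equally well in both arms, there is no inflation. The change should be made because it is cheap and bears directly on the primary endpoint.

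**What to change.** 1. Drop the third part of the patient code (PR05 in place of PR05B) and hold the allocation in a restricted eCRF field.
2. Where the usual ultrasound operator was not part of the surgical team, have the already planned ultrasound result recorded before the arm or the operative record is disclosed to that operator.
3. Give the analyst masked arm labels.
4. State in the protocol that masking is partial, and why: the mesh may be visible on the scan, the physical examination may be done by a surgeon who knows the arm, and patients may disclose it.

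**Cost.** The identifier format in the eCRF changes, and the six codes already issued (Study design section) need re-labelling. No extra visit, procedure or reader is required, because step 2 applies only where a separate operator already does the scan. Where the surgeon does the scan, step 2 offers no protection. Sample size and significance level are unchanged. The remaining downside is that masking stays incomplete.
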